### 6.3. Sample size

Based on the study published by Schweickert et al. where they found that the mean number of days of mechanical ventilation in patients with usual physical therapy was  $6.1 \pm 1.4$  days and in early therapy it was  $3.4 \pm 1.25$  days (32), for an alpha error of 0.05 and a statistical power of 0.8 is considered the following formula:

$$ES = \frac{|\mu_1 - \mu_2|}{\sqrt{DE1^2 - DE2^2/2}}$$

$$ES = \frac{|6.1 - 3.4|}{\sqrt{1.40^2 - 1.25^2/2}}$$

$$ES = \frac{2.7}{\sqrt{3.52/2}}$$

$$ES = 2.03$$

With the effect size calculated ( $ES \approx 0.4463$ ), we can use the formula for the sample size mentioned earlier:

$$n = \frac{2 \left( \frac{Z\alpha}{2} + Z\beta \right)^2 \cdot (\sigma_1^2 + \sigma_2^2)}{ES^2}$$

Where  $\frac{Z\alpha}{2}$  is the critical value corresponding to the alpha significance level /2 to  $\alpha = 0.025$ ,  $\frac{Z\alpha}{2} \approx 2.81$

and  $Z\beta$  is the critical value corresponding to the statistical power beta to  $\beta = 0.90$ ,  $Z\beta \approx 1.28$

The other values we have are the same:

- Mean of group 1 ( $\mu_1$ ) = 6.1 days
- Standard deviation of group 1 ( $\sigma_1$ ) = 1.4 days
- Mean of group 2 ( $\mu_2$ ) = 3.4 days
- Standard deviation of group 2 ( $\sigma_2$ ) = 1.25 days

Effect size ( $ES$ )  $\approx 20.03$  (previously calculated)

Substituting these values into the formula:

$$n = \frac{2 (2.81 + 1.28)^2 \cdot ((1.40)^2 + (1.25)^2)}{(2.03)^2}$$

$$n = \frac{2 (4.09)^2 \cdot (1.96 + 1.56)}{4.13}$$

$$n = \frac{2 (16.72) \cdot (3.52)}{4.13}$$

$$n = \frac{(35.35) \cdot (3.52)}{4.14}$$

$$n = 30.29$$

Rounding:

$$n = 31 \text{ by each group}$$

To the estimated 31 patients per arm, an extra 20% (6 patients per arm) is added to minimize the loss of statistical power in case patients withdraw from the study or there are missing data.

The sample size has also been determined based on the magnitude of the expected effect of mobilization within 48-72 hours of mechanical ventilation, as suggested in the reference study (33), which justifies our choice to evaluate early mobilization at 24 hours versus 72 hours after mechanical ventilation in our study.

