## 2. Problem Statement and Justification

Patients under mechanical ventilation (MV) in the intensive care unit (ICU) exhibit high hospital mortality rates, ranging from 23% to 51%. This mortality is linked to the success of weaning and the incidence of nosocomial infections. Prolonged MV can increase complications in critically ill patients, extending immobility and raising the risk of ventilator-associated pneumonia, further restricting patients. It is argued that early mobility improves MV-related outcomes, such as ventilator duration and ventilator-free days, breaking the vicious cycle of prolonged MV and immobilization. Additionally, early rehabilitation is associated with reduced morbidity and mortality, as well as complications of the disease, ICU length of stay, hospital stay, and rehospitalization rate. Therefore, weaning from MV through early rehabilitation is crucial to improving the prognosis of ICU patients.

Despite the growing evidence on the utility of early rehabilitation for critically ill patients, programs and interest in outcomes vary among studies. Given this diversity, healthcare professionals must assess whether different programs have a similar therapeutic effect and ensure that the prescribed rehabilitation provides benefits consistent with previous literature. Besides the heterogeneity among programs, different countries and institutions face barriers to implementation, such as a shortage of trained rehabilitation personnel and a cultural gap in the ICU. In cases of personnel

shortages and settings with conservative ICU ethics, early rehabilitation is adapted to a sustainable level, including modified programs or less frequent visits.

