| Grip strength at the time of extubation | Grip strength of the dominant hand within 24 hours after extubation                                                                                   | Continuous Quantitative | Kilograms

It will be 0 if the patient dies. |
| Failed extubation                       | Inability to breathe spontaneously in the first 48 hours after removal of the artificial airway and the patient is unable to maintain a patent airway | Qualitative Nominal     | Yes or no                                          |
| NIV POS extubation                      | Post-extubation non-invasive ventilatory support within 48 hours                                                                                      | Qualitative Nominal     | NOT = 0

IF = 1                              |
| Prolonged mechanical ventilation        | Invasive mechanical ventilation longer than 14 days                                                                                                   | Qualitative Nominal     | Yes or no                                          |
| Tracheostomy                            | Need to use a tracheostomy tube.                                                                                                                      | Qualitative Nominal     | Yes or no                                          |
| Adult respiratory distress syndrome     | Bilateral alveolar infiltrates with a PAFI less than 300.                                                                                             | Qualitative Nominal     | Yes or no                                          |

|                              |                                                                                                                   |                     |                                                                                                                                                                                                                                                    |
|------------------------------|-------------------------------------------------------------------------------------------------------------------|---------------------|----------------------------------------------------------------------------------------------------------------------------------------------------------------------------------------------------------------------------------------------------|

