A detailed exploration will be conducted through a sensitivity analysis of possible interactions between identified subgroups, according to the RASS scale, protocol adherence, and other relevant variables, to deepen the understanding of any joint influence that may affect the study results. If no statistically significant differences are identified through regression analyses, a post-hoc analysis will be conducted to assess whether the recruited sample size was adequate to detect possible differences between the established subgroups. This additional analysis will allow adjusting the interpretation of the results and provide valuable information on the validity of the obtained conclusions.

Finally, an independent data monitoring committee will be established to conduct interim reviews of the sample size, allowing adjustments based on variations in event rates observed during the study, thus ensuring adequate statistical power throughout its execution.

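### Section 6.3: 31 per arm does not follow from the declared alpha and power, and the calculation sizes a difference in means rather than the primary Cox/log-rank analysis, so the stated power has no basis

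*Protocol*

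**What the plan says.** Section 6.3 takes mean ventilation times of 6.1 ± 1.4 days (usual therapy) and 3.4 ± 1.25 days (early therapy) from a cited trial and sets the size "for an alpha error of 0.05 and a statistical power of 0.8 is considered the following formula".

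It computes a standardised effect size of 2.03. The printed formula has a minus sign between the variances. It continues that "we can use the formula for the sample size mentioned earlier", there giving the effect size as 0.4463 and, a few lines later, as 20.03. The value 2.81 "is the critical value corresponding to the alpha significance level /2 to" 0.025, and 1.28 is given for 0.90. The substitution is "n = \frac{2 (2.81 + 1.28)^2 \cdot ((1.40)^2 + (1.25)^2)}{(2.03)^2", which the section evaluates as 30.29 and rounds to 31.

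For losses: "To the estimated 31 patients per arm, an extra 20% (6 patients per arm) is added", giving 37 per arm and 74 in total.

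The main outcome in 6.6 is time from intubation to extubation. Section 6.13 addresses the primary objective with a survival analysis: univariable Cox regression on treatment group and a log-rank test. It also sets up an independent committee to review sample size at interim against observed event rates. It says that, if the regressions show nothing significant, "a post-hoc analysis will be conducted to assess whether the recruited sample size was adequate to detect possible differences"; that sentence goes on to name the subgroups.

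**The concern.** The section declares one pair of error rates and computes with another, so its result cannot be traced to its inputs. Separately, the power of a log-rank or Cox comparison depends on the number of extubations and the hazard ratio. Section 6.3 mentions neither, so even a correct two-means calculation would not give the power of the primary analysis.

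Two things are at stake. Readers will take 37 per arm as giving 80% power on the primary analysis, and nothing in the document supports that. The interim review is meant to react to departures in event rates, but no planned rate exists to compare with.

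**Working it through.** **Inputs.** From 6.3: means 6.1 and 3.4, SDs 1.4 and 1.25, alpha 0.05, power 0.8. The use of alpha/2 implies a two-sided test. Allocation is 1:1 (6.4).

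**The plan's own figure**
- Effect size: pooled SD = √((1.96 + 1.5625)/2) = 1.327, and 2.7/1.327 = 2.03. This needs a plus sign. The section's own 3.52 is the sum, so the minus sign is a misprint.
- Printed expression: 2 × 4.09² × 3.5225 / 2.03² = 2 × 16.73 × 3.5225 / 4.121 = 28.6.
- The section reaches 30.29 through slips. 2 × 16.72 is 33.44, not 35.35. Even 35.35 × 3.52 / 4.14 is 30.06.

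**Critical values**
- z(0.975) = 1.96. If 0.025 were itself halved, z(0.9875) = 2.24. Neither is 2.81, which corresponds to a two-sided alpha of 0.00495.
- 80% power needs 0.84. The 1.28 used is for 90%.

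**Formula.** The expression multiplies by (σ₁² + σ₂²) and divides by the square of an effect already divided by the SD, so the variance enters twice. The standard form is n = 2(z_α/2 + z_β)²/ES² per arm:

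| Two-sided alpha 0.05 | 80% power | 90% power |
|---|---|---|
| Standard formula, ES 2.03 | 3.8, so 4 | 5.1, so 6 |
| Exact t-test | 5 | 7 |
| Printed formula with correct z | 13.4 | 18.0 |

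None gives 31. With the stated means and SDs, t-test power at 31 per arm exceeds 99.9%.

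**Losses.** 37 × 0.8 = 29.6, fewer than 31. Keeping 31 after a 20% loss needs 31/0.8 = 38.75, so 39 per arm.

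**Primary analysis.** The Schoenfeld approximation gives power = Φ(√D × ln HR / 2 − 1.96) for D events. The protocol states no hazard ratio, so two readings of its own means are shown, assuming that every patient is extubated:
- Exponential times: HR = 6.1/3.4 = 1.79, ln HR = 0.5845. With D = 62: 7.874 × 0.2922 − 1.96 = 0.34, power 63%. With D = 74: 8.602 × 0.2922 − 1.96 = 0.55, power 71%. Simulated log-rank power was 64% and 67%. For 80% power, 92 events are needed.
- Normal times with the stated SDs: simulated log-rank power was 100% at 31 per arm (1,000 runs).

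**Detectable hazard ratio at 80% power**, HR = exp(2 × 2.80/√D):

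| Extubations | Basis | HR |
|---|---|---|
| 74 | all randomised patients | 1.92 |
| 62 | 31 per arm, all extubated | 2.04 |
| 57 | 74 × 0.77 (assumption) | 2.10 |
| 36 | 74 × 0.49 (assumption) | about 2.5 |

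The last two rows borrow the range in section 2, "high hospital mortality rates, ranging from 23% to 51"%, as if every such death meant no extubation. The base is 74 because 6.8 keeps all assigned patients in the main analysis.

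**The case against.** The strongest reply is that the errors enlarge the trial. The inflated critical value and the double variance raise the figure from 4–7 to 31 per arm, so on the protocol's own inputs the trial is more than large enough. That stands, and it limits the point: a reader might infer that 74 patients are too few or that only a very large effect is detectable, and the documents do not show this.

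Other stronger readings also fail:
- **Effect sizes 0.4463 and 20.03, and the minus sign.** None enters the substituted calculation, so a sample size or power derived from 0.4463 would describe a number that the plan does not use. They are errors to clean up.
- **The 14-day outcome.** The variable table defines prolonged ventilation as "Invasive mechanical ventilation longer than 14 days", and under a normal distribution with mean 6.1 and SD 1.4 this would essentially never occur. But the protocol does not assume normality; 6.13 provides for Mann-Whitney. Listing an outcome also does not assert its frequency.
- **Mortality as non-extubation.** The section 2 range is for ventilated ICU patients in general. This trial requires a Barthel index of at least 70 and excludes cardiac arrest, COPD and life expectancy under 180 days, and patients can die after extubation. Those rows are upper bounds on non-extubation.
- **Post-hoc adequacy analysis.** It is worded for subgroups and does not say that observed effects will be plugged in, so it is a secondary matter.

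It may also be said that the 20% is added only to lessen the loss of power and that 6.10 merely says a null trial could count as a failure to demonstrate effectiveness. Both are fair. Neither supplies the missing link between 31 per arm and a stated power, and the interim review does not supply the missing hazard ratio.

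**Conclusion.** The point holds in this form. The 31 per arm cannot be obtained from the declared alpha of 0.05 and power of 0.8 with the stated means and SDs; those give 4 to 5 per arm (6 to 7 at 90%). The section's own expression, with its own wrong critical values, gives 28.6. The calculation also concerns a different analysis from the primary one.

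The power of the primary analysis is therefore undetermined. It runs from about 63–71% (exponential times, stated means, 62 to 74 extubations) to near 100% (normal times, stated SDs). Both figures assume that all patients are extubated. Whether the quoted ± values are SDs of individual times cannot be checked from the protocol. If the true SD were larger (an assumption), 31 per arm would keep 80% t-test power for a 2.7-day difference only up to an SD of about 3.8 days (2.7/0.7116).

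**What to change.** Keep the planned 74 patients, subject to the interim sample-size review in 6.13, and rewrite 6.3:

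1. State one two-sided alpha of 0.05.
2. Remove the present derivation, including the stray effect sizes and the minus sign, and both power statements.
3. State the hazard ratio detectable with 80% power by Cox/log-rank at the expected number of extubations: 1.92 at 74 events, 2.04 at 62, 2.10 at 57 and about 2.5 at 36. Label the last two as assumptions that apply 23% and 51% non-extubation to all 74 patients.
4. State the assumed event rate, so that the interim review has a reference.
5. Describe the extra 20% as an allowance, since it does not preserve 31 per arm after a 20% loss.

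In 6.13, say that a non-significant primary result will be interpreted from the hazard ratio and its 95% confidence interval. As a secondary change, do the same for the subgroups in place of the post-hoc sample-size adequacy analysis.

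The cost is protocol wording, with no additional patients. The protocol gives up a single power figure and gains a statement that can be checked.

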#### 6.4. Sampling and Randomization

Patients who meet the inclusion criteria will be assigned, through stratified randomization by sex and age group (under 65 years and over 65 years), to one of the two study groups at a 1:1 ratio (sampling stratified randomized). The number of resulting strata corresponds to 4. Randomization will be applied to each stratum. This type of sampling and randomization reduces possible imbalances and increases statistical power, considering that the number of participants per arm is 37. Allocation concealment will be carried out using sealed and sequentially numbered opaque envelopes, which will be in the Intensive Care Unit office on the fourth floor of the expansion building. A record of the person who opened the envelope will be kept by Good Clinical Practice guidelines.

#### 6.5. Intervention

Early multimodal therapy is defined as the set of therapeutic maneuvers performed by the physiotherapy, speech therapy, respiratory therapy, and occupational therapy team within 24 hours of orotracheal intubation. In contrast, late multimodal therapy is characterized by the same type of maneuvers performed by the same disciplinary group at 72 hours of orotracheal intubation.

Multimodal therapy will be carried out according to the results of the Richmond Agitation-Sedation Scale (RASS). All personnel involved in our study will receive specific training in the accurate assessment of this scale, to reduce intra- and inter-evaluator variability in the application of the intervention.

It is clarified that the set of therapeutic maneuvers carried out in both groups is an integral part of the standard care provided to our patients in the intensive care unit. Additionally, both groups will receive all the medical interventions that would normally be applied during their ICU stay, regardless of their participation in the study. This ensures consistency in care during the study.

Standard management in our ICU involves specialized and continuous care for patients with severe illnesses or those requiring constant monitoring. These include:

**Continuous Monitoring:** Continuous monitoring of vital signs such as heart rate, blood pressure, respiratory rate, and oxygen saturation to detect immediate changes in the patient's condition.

**Life Support:** Providing advanced life support, which may include oxygen administration, mechanical ventilation, medications to maintain blood pressure, and other treatments necessary to maintain physiological stability.

**Pain and Sedation Management:** Adequate management of pain and sedation to ensure patient comfort and facilitate necessary medical procedures.

**Infection Prevention and Treatment:** Implementation of infection control measures to prevent the spread of diseases, as well as the use of antibiotics and other specific treatments to combat infections.

**Specialized Nutrition:** Providing enteral or parenteral nutrition according to the individual needs of patients, especially if they cannot feed orally.

**Fluid Management:** Carefully controlling fluid and electrolyte levels to maintain fluid balance and correct imbalances if necessary.

**Multidisciplinary Coordination:** Promoting collaboration among healthcare professionals, including doctors, nurses, therapists, and other specialists, to ensure comprehensive and personalized care.

**Communication with Family Members:** Maintaining clear and regular communication with the patient's family, providing information about the patient's condition, and offering emotional support.

**Crisis Management:** Being prepared to address emergencies and make quick and effective decisions in response to acute changes in the patient's condition.

Interventions will be performed daily once the patient has been included in the study and will be carried out according to the expert consensus recommending mobilization maneuvers when the patient has an FIO2 less than or equal to 0.6, a percutaneous oxygen saturation greater than or equal to 90%, a respiratory rate less than 30 breaths per minute, and a PEEP less than or equal to 10 cmH2O.

These maneuvers will be performed until the patient is discharged (defined as the moment when the intensivist determines that the patient can be transferred to hospitalization or discharged from the hospital) from the ICU.

### **Speech Therapy Group Interventions**

The speech therapy group will assess the sedation level using the Richmond Agitation-Sedation Scale (RASS). For patients who are unresponsive or have a RASS score of -2 or lower, passive/assisted proprioceptive speech therapy will be carried out. This involves procedures such as craniofacial alignment, mandibular mobilization, lingual mobilization, cervical mobilization, pharyngeal reflex stimulation, orofacial muscle activation, oral mucosa hydration, and supra- and infrahyoid muscle activation.

On the other hand, for patients with a RASS score between -1 and +1, active/assisted neuromuscular praxis speech therapy will be applied. This involves the active performance of procedures such as craniofacial alignment, mandibular mobilization, lingual mobilization, cervical mobilization, pharyngeal reflex stimulation, orofacial muscle activation, oral mucosa hydration, and active supra- and infrahyoid muscle activation. The details of each intervention are provided in Annex 1.

### **Physical Therapy Group Interventions**

From the field of physical therapy, an assessment will be conducted using the Richmond Agitation-Sedation Scale (RASS). For patients who are unresponsive or have a RASS score of -2 or lower, a passive/assisted proprioceptive intervention will be applied. This involves techniques such as facilitation of muscle fiber recruitment, inhibitory reflex positioning, particular mobilization, joint loading, and approximation, as well as activation of joint receptors.

For patients with a RASS score between -1 and +1, motor activation intervention using proprioceptive neuromuscular facilitation techniques will be performed. Additionally, electrostimulation will be applied to large muscle groups and accessory respiratory and diaphragmatic muscles. This is done to promote intentional movement and plan and execute dynamic motor patterns that help trigger support and balance reactions, to promote maximum functional development in critically ill patients. A detailed description of the intervention is provided in Annex 1.

For patients who can tolerate motor activation intervention (RASS between -1 and +1), bed mobility exercises, transfer exercises from bed to chair or chair to bed, pre-gait exercises, and finally gait training will be performed. The progression will depend on the patient's tolerance and stability.

### **Respiratory therapy group interventions**

The intervention performed by the respiratory therapy group is divided into three main categories:

**Airway Clearance Techniques:** Methods to ensure the airway remains clear of obstructions, such as mucus or foreign bodies.

**Lung Re-expansion Techniques:** Procedures aimed at improving lung expansion and preventing atelectasis.

**Respiratory Muscle Strengthening Techniques:** Exercises and interventions designed to enhance the strength and endurance of the respiratory muscles.

The detailed description of the interventions performed by the respiratory therapy group is comprehensively described in Annex 1.

### **Occupational therapy group interventions**

To carry out this process, if the patient presents a level of consciousness with a RASS score of -3 or lower, multisensory stimulation activities will be performed. These activities include tactile, proprioceptive, vestibular, gustatory, auditory, and olfactory stimulation, fully assisted by the therapist. These activities should be related to simulated daily life tasks and include upper limb movement patterns, with an emphasis on primary patterns such as hand-to-head, hand-to-mouth, homolateral hand, contralateral hand, and hand-to-perineum, in addition to caring for the joints and feet.

For patients with a RASS score between -2 and -1, interventions will be performed in a passive-assisted manner and will focus on sensory stimulation, along with cognitive feedback to recognize elements and perform daily tasks. Instructions will be given with a maximum of two commands, using integral movement patterns such as reaching, grasping, releasing, and throwing, with an emphasis on frontal and lateral planes in the bed.

When the patient has a RASS score of 0 to +1, the intervention focuses on the patient's active and autonomous participation in activities, with minimal support from the therapist according to the patient's tolerance. Emphasis is placed on autonomy in daily tasks, integrating sensory and cognitive commands of low, medium, and high complexity, using upper limb movement patterns previously worked on in all anatomical planes, either in bed, at the edge of the bed, or in a chair, depending on the progress in rehabilitation.

For patients with a RASS score of +2 or higher, therapeutic sessions focus on behavioral and environmental modulation, including the physical and family environment. Connection with the environment is promoted through inhibitory multisensory stimulation activities and cognitive stimulation oriented towards meaningful tasks, with active assistance in bed. Additionally, the family is educated on the importance of maintaining continuous orientation, and sensory stimuli are enriched to converge on a common task, using visual, auditory, tactile, and proprioceptive stimuli (see Annex 1).

